#### **4) Sophisticated safety monitoring method and slow climbing speed**

The major adverse effects of OXM targets are gastrointestinal and easy to monitor. 2.5 mg is the dose that has been verified to be safe for healthy people in the United States. The (typical) maximum plasma concentration (Cmax) produced by 2.5 mg and 3mg in Chinese subjects was < the drug concentration level that has been validated as safe (2.5 mg) in healthy subjects in the United States. Compared with the previous dose group, the increase rate of dose group was 20%, and the increase rate was slow.

#### **5) Potential for better therapeutic benefit**

Studies in US subjects have shown that the weight loss effect of IBI362 increases with increasing drug exposure. The body weight loss data for Chinese subjects also showed a dose-dependent trend. While controlling for safety, it is necessary to explore weight loss activity at higher exposures.

### **3.2 Phase Ib/II Study Design**

#### **3.2.1 Overall Study Design**

This study has enrolled 36 overweight or obese subjects (Cohort 1, Cohort 2, and Cohort 3) with weight change of less than 5% controlled by diet and exercise for at least 12 weeks. All subjects were safe and well tolerated (see Section 1.3. 2 and 1.3. 3 for details). Based on the current PK data of subjects in Cohorts 1-3 showing that the plasma concentration in Chinese overweight/obese population is lower than the plasma concentration prespecified in the study, Cohort 4 and Cohort 5 will be further explored, with 12 subjects in each group, and an estimated total of 24 subjects will be added based on the Chinese PK data of IBI362. The entire trial period consisted of a 3-week screening period, a 12-to 16-week double-blind treatment period, and an 8-week follow-up period after the last dose.

The double-blind treatment phase was divided into five cohorts, Cohort 1 (n=12), Cohort 2 (n=12), Cohort 3 (n=12), Cohort 4 (n=12), and Cohort 5 (n=12), and subjects in each cohort were randomized in a 2: 1 ratio to IBI362 treatment (n=8) and placebo (n=4). The SC dosing regimens of IBI362 or placebo in Cohort 1, Cohort 2, Cohort 3, Cohort 4, and Cohort 5 are described as follows:

#### **Cohort 1**

The starting dose is 1.0 mg once weekly for consecutive 4 weeks. If the subject is well tolerated #, the dose will be up-titrated to 2.0 mg once weekly for consecutive 4 weeks. The tolerability will be observed again. If the subject is well tolerated #, the dose will be up-titrated to 3.0 mg once weekly for consecutive 4 weeks. (The dose will be increased by 1mg every 4 weeks to the target dose).

## **Cohort 2**

The starting dose is 1.5 mg, administered once a week for consecutive 4 weeks. If the subject is well tolerated #, the dose will be up-titrated to 3.0 mg, administered once a week for consecutive 4 weeks. The tolerability of the subject will be observed again. If the subject is well tolerated #, the dose will be up-titrated to 4.5 mg, administered once a week for consecutive 4 weeks (the dose will be increased by 1.5 mg every 4 weeks to the target dose).

1If subjects in Cohort 2 are intolerant to 3.0 mg or 4.5 mg, the dose should be adjusted according to the criteria in Table 1.

## **Cohort 3**

The subjects in Cohort 2 can only start the administration after the subjects in Cohort 2 have completed the administration of 1.5 mg for 4 weeks and are well tolerated; If 1.5 mg is not tolerated by subjects in Cohort 2, 2.0 mg and higher will not be explored for subjects in Cohort 3.

In this cohort, the starting dose is 2.0 mg once weekly for consecutive 4 weeks. If the subject has good tolerance #, the dose will be increased to 4.0 mg once weekly for consecutive 4 weeks. The tolerability will be observed again. If the subject has good tolerance #, the dose will be increased to 6.0 mg once weekly for consecutive 4 weeks. (The dose will be increased by 2mg every 4 weeks to the target dose).

## **Cohort 4**

The starting dose of the subjects is 2.5 mg, once a week, after continuous administration for 4 weeks; If the subject is well tolerated #, the dose will be up-titrated to 5.0 mg once a week for consecutive 4 weeks; Observe the tolerance of the subjects again. If the tolerance is good #, the dose will be increased to 7.5 mg once a week for consecutive 4 weeks; Observe the tolerability of the subjects again. If the tolerability is good #, the dose will be increased to 10.0 mg once a week for consecutive 4 weeks (the dose will be increased by 2.5 mg every 4 weeks to the target dose).

## **Cohort 5**

The starting dose of the subjects is 3.0 mg, once a week, after continuous administration for 4 weeks; If the subject is well tolerated #, the dose will be up-titrated to 6.0 mg, once a week for consecutive 4 weeks; Observe the tolerability of the subjects again. If the tolerability is good #, the dose will be increased to 9.0 mg once a week for consecutive 4 weeks (increase the dose by 3.0 mg every 4 weeks to the target dose).

(I) Stop criteria for dose escalation: If any of the following criteria are met, the dose escalation will be terminated.

- Heart rate > 100 beats per minute occurred in > 50% of subjects taking IBI362 within

the same dose.

- Occurrence of at least one treatment-related serious adverse event (other than those expected to be related to the pharmacological properties of IBI362, such as hypoglycemia).
- "No less than 50% of subjects experienced symptomatic hypoglycemic events with plasma glucose levels  $< 2.8$  mmol/L at a given dose level, and these events were considered related to IBI362."
- No less than 2 subjects who receive IBI362 develop persistent (more than one week) symptoms characteristic of acute pancreatitis.
- Non-serious AEs of severe intensity that are related to IBI362 (refer to Section 7.3 of the protocol) occurring in no less than 2 subjects in the same dose group, regardless of whether or not the event is associated with the same organ or system (other than gastrointestinal effects).

Note: In case of AE related to dose escalation stop, please report to the sponsor as per Appendix 6.

## **(II) Intolerance criteria for a single subject:**

- If venous plasma glucose  $< 2.8$  mmol/L; Or if the venous plasma glucose does not reach the standard of  $< 2.8$  mmol/L, but the symptoms of hypoglycemia are obvious and cannot be recovered spontaneously (within 15min), and the re-test before the next dose still meets the above standard, it is considered that the patient is intolerant at this dose;
- If there are other intolerance conditions related to the study drug that the investigator considers to be related to the study drug, and the investigator thinks it is necessary to stop the exploration of the subject at this dose after discussion with the sponsor, this case is considered to be intolerable at this dose.

### **3.2.2 Actions Taken to Avoid Bias**

The possible bias was not avoided. The double-blind placebo-controlled study was used in this study. Meanwhile, the safety and efficacy measurements were objective measurements, and the artificial bias was small.

### **3.2.3 Definition of End of Study**

The end of the study was defined as the time when the last subject completed the last visit.

## **4 Study Population**

Subject Eligibility: Deviations from eligibility criteria may impact the scientific integrity of the study, regulatory acceptability, and/or subject safety and are not permitted. Therefore, subjects must meet the protocol-specified criteria.

#### 4.1 Inclusion Criteria

Subjects met all of the following criteria to be included in the study:

1. Age 18 ~ 75 years (both inclusive), male or female;
2. Obese:  $BMI \geq 28.0 \text{ kg/m}^2$ ; Or overweight:  $24 \leq BMI < 28.0 \text{ kg/m}^2$  with at least one of the following manifestations: i. Strong appetite, unbearable hunger before meal, and more food intake per meal; ii. Patients with one or more of pre-diabetes (impaired fasting glucose and/or impaired glucose tolerance), hypertension, dyslipidemia (see Annex 4 for reference standards), and fatty liver (within 6 months prior to screening); iii. Combined weight-bearing joint pain; iv. Obesity-induced dyspnea or obstructive sleep apnea syndrome;
3. Controlled by diet and exercise alone for at least 12 weeks at screening, with body weight change of less than 5%;
4. Able to understand the procedures and methods of this study, willing to strictly comply with the clinical trial protocol to complete this trial, and voluntarily sign the informed consent form.

#### 4.2 Exclusion Criteria

Subjects will be excluded from the study if they meet any of the following criteria:

1. Subjects who are suspected by the investigator to be allergic or have allergic constitution to the study drug or ingredients;
2. Use of any of the following medications or treatments prior to screening:
  - 1) Previous use of GLP-1 receptor (GLP-1R) agonists or GLP-1R/GCGR agonists;
  - 2) Use of drugs that affect body weight within 3 months prior to screening, including systemic steroids (intravenous, oral or intra-articular administration), metformin, SGLT2 inhibitors, thiazolidinediones (TZDs), tricyclic antidepressants, psychiatric drugs or sedative drugs (such as imipramine, amitriptyline, mirtazapine, paroxetine, phenelzine, chlorpromazine, thioridazine, clozapine, olanzapine, valproic acid, valproic acid derivatives, lithium salts);
  - 3) Use of Chinese herbal medicine or health products affecting body weight within 3 months prior to screening.
  - 4) Have used or are currently using weight loss drugs within 3 months prior to screening, such as: sibutramine hydrochloride, orlistat, phentermine, phenylpropanolamine, chlorpheniramine, phentermine, bupropion, lorcaserin, phentermine/topiramate mixture, naltrexone/bupropion mixture, etc.;
  - 5) Participation in other clinical trials (treated with an investigational drug) within 3 months prior to screening.

3. History or evidence of any of the following prior to screening:
- 1) Subjects diagnosed with diabetes mellitus according to WHO1999 criteria;
  - 2) Fasting venous blood glucose  $\geq 7.0$  mmol/L at screening or venous blood glucose  $\geq 11.1$  mmol/L 2 hours after 75g oral glucose tolerance test (OGTT) glucose load (for subjects with fasting blood glucose of 6.1-7.0 mmol/L at screening, venous blood glucose 2 hours after OGTT glucose load should be collected for confirmation);
  - 3) Subjects with retinopathy in the past or at screening;
  - 4) Obesity caused by secondary diseases or drugs, including: increased cortisol hormone (such as Cushing's syndrome), obesity caused by pituitary gland and hypothalamus injury, obesity caused by reduction/withdrawal of weight-reducing drugs, etc.;
  - 5) Previous bariatric surgery or acupuncture for weight loss within 1 year before screening;
  - 6) History of depression in the past; Or have a history of severe mental illness in the past, such as: schizophrenia, bipolar disorder, etc.;
  - 7) Uncontrolled hypertension at screening after treatment with antihypertensive drugs for at least 4 weeks, defined as: systolic blood pressure  $> 140$ mmHg and/or diastolic blood pressure  $> 100$ mmHg;
  - 8) Systolic blood pressure  $< 90$ mmHg and/or diastolic blood pressure  $< 50$ mmHg at screening;
  - 9) History of malignancy (except cured basal cell carcinoma of the skin and carcinoma in situ of the cervix) at the time of screening;
  - 10) Heart-related diseases (such as angina pectoris, myocardial infarction, cardiomyopathy, acute and chronic heart failure, etc.) at screening;
  - 11) Hemorrhagic or ischemic stroke or transient ischemic attack within 6 months prior to screening;
  - 12) History of thyroid C-cell carcinoma, MEN (multiple endocrine neoplasia) 2A or 2B syndrome, or relevant family history at screening;
  - 13) History of acute or chronic pancreatitis, gallbladder disease, or pancreatic injury at screening;
  - 14) Chronic gastrointestinal disease, systemic disease that may affect gastrointestinal motility at screening, or use of drugs that may alter gastrointestinal motility, appetite or absorption within 3 months prior to screening;

- 15) Existence of limb deformity or disability, unable to accurately determine height, weight and other indicators;
  - 16) Major and medium-sized surgery, severe trauma, severe infection within 1 month prior to screening, which is not suitable to participate in the investigator as judged by the investigator;
  - 17) Previous suicidal tendency or suicidal behavior;
  - 18) Anticipated surgery during the trial, except for outpatient surgery that has no effect on the safety of subjects and trial results as judged by the investigator;
  - 19) Subjects who are positive for human immunodeficiency virus (HIV) antibody or hepatitis B surface antigen (HBsAg) or hepatitis C (HCV) antibody or syphilis antibody at screening;
  - 20) History of alcohol abuse within 1 month prior to screening. Average weekly alcohol intake of more than 21 units for men and 14 units for women, or unwillingness to stop drinking 24 hours before the dosing day and throughout the study (1 unit = 360ml of beer, or 150ml of red wine, or 45ml of distilled spirits/liquor);
  - 21) Positive urine screening test for drugs and drugs of abuse at screening.
4. Any laboratory test indicator meeting the following criteria (if there is a clear reason for retest at screening, it can be retested within one week, and the investigator should record the reason for retest):
- 1) Serum calcitonin  $\geq 15$  ng/L at screening;
  - 2) Alanine aminotransferase  $\geq 2.0 \times \text{ULN}$  and/or aspartate aminotransferase  $\geq 2.0 \times \text{ULN}$  and/or total bilirubin  $\geq 1.0 \times \text{ULN}$  and/or alkaline phosphatase  $\geq 2.0 \times \text{ULN}$  at screening;
  - 3) Glomerular filtration rate eGFR  $< 60$  mL/min/1.73 m^2 at screening, as estimated by the CKD-EPI equation (see Appendix 2);
  - 4) Abnormal thyroid function (FT3, FT4, or TSH) at screening;
  - 5) Fasting triglycerides  $\geq 5.64$  mmol/L (500 mg/dl) at screening, if the subject is on lipid-modifying therapy, the drug dose must be stable for 30 days prior to screening;
  - 6) Blood amylase or lipase  $> 2.0 \times \text{ULN}$  at screening;
  - 7) International normalized ratio (INR) of prothrombin time greater than the upper limit of normal at screening.
5. Heart rate  $< 50$  beats/min or  $> 90$  beats/min on 12-lead ECG at screening;

6. Subjects with the following clinically significant 12-lead electrocardiograms (ECGs) abnormalities at screening: second or third degree atrioventricular block without a pacemaker, long QT syndrome or QTcF > 450ms (see Appendix 3 for calculation formula), PR interval < 120ms or PR interval > 220ms, QRS > 120ms, left or right bundle branch block, pre-excitation syndrome, or serious arrhythmia requiring treatment;
7. Pregnant or lactating females, males or females of childbearing potential not willing to use contraception throughout the study;
8. Blood donation and/or blood loss  $\geq$  400 mL or bone marrow donation within 3 months prior to screening, or presence of hemoglobinopathy, hemolytic anemia, sickle cell anemia, or hemoglobin < 110g/L (male) or < 100g/L (female);
9. The subject has any other factors that may affect the efficacy or safety evaluation of this study, and is not suitable for participation in this study in the opinion of the investigator.

#### **4.3 Restrictions during the Study**

- Subjects should not donate blood during their participation in this study and within 8 weeks after the last dose;
- Men or women of childbearing potential must use contraception during the study and for 8 weeks after the last dose.
- Not allowed to participate in other clinical trials;
- During the trial, the original diet, exercise and lifestyle were maintained steadily, and binge eating and strenuous exercise were taboo;
- Alcohol consumption was prohibited during the trial.

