| Study duration (weeks)                                               | -3 ~ 0                        | 1                                          | 2   | 3   | 4   |    | 5   |    | 6   | 7   | 8   |     | 9   |     | 10  | 11  | 12  |     |     | 13  | 20        |                  |
| Study Duration (days)                                                | -21 ~-1                       | 1                                          | 8   | 15  | 22  | 23 | 29  | 30 | 36  | 43  | 50  | 51  | 57  | 58  | 64  | 71  | 78  | 79  | 80  | 85  | 134       |                  |
| Window (days)                                                        | -                             | -                                          | ± 2 | ± 2 | ± 2 | -  | ± 2 | -  | ± 2 | ± 2 | ± 2 | -   | ± 2 | -   | ± 2 | ± 2 | ± 2 | -   | -   | ± 2 | ± 3       |                  |
| Serum calcitonin                                                     | X                             |                                            |     |     |     |    |     |    |     |     |     |     |     |     |     |     |     |     |     | X   |           | X                |
| Blood pregnancy test                                    | X                             |                                            |     |     |     |    | X   |    |     |     |     |     | X   |     |     |     |     |     |     | X   |           | X                |
| Thyroid function                                        | X                             |                                            |     |     |     |    |     |    |     |     |     |     |     |     |     |     |     |     |     |     |           |                  |
| Glycosylated hemoglobin                                 | X                             | ●                                          |     |     |     |    |     |    |     |     |     |     |     |     |     |     |     |     |     | ●   |           | ●                |
| OGTT                                                    | X                             |                                            |     |     |     |    |     |    |     |     |     |     |     |     |     |     |     |     |     |     |           |                  |

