16. Dual-energy X-ray (DEXA) and abdominal MRI are recommended to be performed at sites where conditions permit. DEXA method determination: The subject lies on the examination table, uses the DEXA standard mode, the scanning frame moves from the head side to the foot side, and scans. The scanning conditions were voltage ( $76 \pm 3$ ) KV and current 0.15 mA, tube voltage of two X-rays was 38 V and 70 KV, respectively, the scanning particle range was 197 cmx60 ca, the width was fixed at 60 cm, the scanning time was about 5 min, and the radiation absorber was 0.002 mGy. At the end of the measurement, DEXA device automatically recorded the fat weight of the whole body, waist and buttocks and other parameters, and calculated the waist-buttock fat ratio: waist fat weight (g)/buttock fat weight (g). PLODIGY dual-energy X-ray absorptiometry (Lunar, GE Company, USA) was recommended as the equipment used.
17. PCSK9 and FGF21 test: The blood collection points are V2 visit (D1), V20 visit (D85) and unscheduled, 3 mL of whole blood will be collected at each blood collection point. See the central laboratory manual for detailed operation procedures.
18. Immunogenicity sampling points: Week 1 (within 1h before dosing on Day1), Week 5 (within 1h before dosing on Day29), Week 9 (within 1h before dosing on Day57), Week 13 (168 h  $\pm$  12 h after dosing on Day78) and Follow-up Visit on Week 20. If a subject withdraws early, whenever possible, 1 immunogenicity sample will be collected at the early withdrawal visit. 5 mL of whole blood will be collected at each blood collection point. Detailed procedures will be described in the central laboratory manual.
19. **33**Refer to Table 3-1 and Table 3-2 for PK/PD sampling points.
20. In this study, fasting blood collection was required to be fasted for at least 8 hours, and the drug was administered after fasting blood collection and then fed.

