| Window (days)                                             | -                             | -                             | ±2 | ±2 | ±2 | -  | ±2 | -  | ±2 | ±2  | ±2  | -   | ±2  | -   | ±2  | ±2  | ±2  | -   | -   | ±2  | -   | ±2  | ±2  | ±2  | -   | -   | -   | ±2               | ±3  | ±3               |   |
| Hip circumference                             | X                             | X                             |    |    |    |    | X  |    |    |     |     |     | X   |     |     |     |     |     |     | X   |     |     |     |     |     |     |     | X                | X   | X                | X |
| Laboratory tests                              | X                             |                               |    |    |    |    | X  |    |    |     |     |     | X   |     |     |     |     |     |     | X   |     |     |     |     |     |     |     | X                |     | X                | X |
| Alcohol breath test                                       | X                             |                               |    |    |    |    |    |    |    |     |     |     |     |     |     |     |     |     |     |     |     |     |     |     |     |     |     |                  |     |                  |   |
| Urine Drug Screen                             | X                             |                               |    |    |    |    |    |    |    |     |     |     |     |     |     |     |     |     |     |     |     |     |     |     |     |     |     |                  |     |                  |   |
| 12-lead ECG                                   | X                             | X                             | X  | X  | X  | X  | X  | X  | X  | X   | X   | X   | X   | X   | X   | X   | X   | X   | X   | X   | X   | X   | X   | X   | X   | X   | X   | X                | X   | X                | X |
| Serological testing for infectious diseases  | X                             |                               |    |    |    |    |    |    |    |     |     |     |     |     |     |     |     |     |     |     |     |     |     |     |     |     |     |                  |     |                  |   |

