| Serum calcitonin                                          | X                             |                               |    |    |    |    |    |    |    |     |     |     |     |     |     |     |     |     |     |     |     |     |     |     |     |     |     | X                |     |                  | X |
| Blood pregnancy test                         | X                             |                               |    |    |    |    | X  |    |    |     |     |     | X   |     |     |     |     |     |     | X   |     |     |     |     |     |     |     | X                |     |                  | X |
| Thyroid function                             | X                             |                               |    |    |    |    |    |    |    |     |     |     |     |     |     |     |     |     |     |     |     |     |     |     |     |     |     | X                |     |                  |   |

| Study Phases and Procedures                                          | Screening Period  | Double-Blind Treatment Period |    |    |    |    |    |    |    |     |     |     |     |     |     |     |     |     |     |     |     |     |     |     |     |     |     | Safety Follow-up |     | Early Withdrawal |   |   |
|----------------------------------------------------------------------|-------------------------------|-------------------------------|----|----|----|----|----|----|----|-----|-----|-----|-----|-----|-----|-----|-----|-----|-----|-----|-----|-----|-----|-----|-----|-----|-----|------------------|-----|------------------|---|---|
| Study Visits                                                         | V1                            | V2                            | V3 | V4 | V5 | V6 | V7 | V8 | V9 | V10 | V11 | V12 | V13 | V14 | V15 | V16 | V17 | V18 | V19 | V20 | V21 | V22 | V23 | V24 | V25 | V26 | V27 | V28              | V29 | V30              |   |   |
| Study duration (weeks)                                               | -3 ~ 0                        | 1                             | 2  | 3  | 4  |    | 5  |    | 6  | 7   | 8   |     | 9   |     | 10  | 11  | 12  |     |     | 13  |     | 14  | 15  | 16  |     |     |     | 17               | 20  | 24               |   |   |

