| Window (days)                                                                 | -                         | -                             | ±
2 | ±
2 | ±
2 | -      | ±
2 | -      | ±
2 | ±
2  | ±
2  | -       | ±
2  | -       | ±
2  | ±
2  | ±
2  | -       | -       | -       | ±
2  | ±
3                  | ±
3  |                         |
| 12-lead ECG                                                       | X                         | X                             | X      | X      | X      | X      | X      | X      | X      | X       | X       | X       | X       | X       | X       | X       | X       | X       | X       | X       | X       | X                       | X       | X                       |
| Serological testing
for infectious
diseases                | X                         |                               |        |        |        |        |        |        |        |         |         |         |         |         |         |         |         |         |         |         |         |                         |         |                         |
| Serum calcitonin                                                              | X                         |                               |        |        |        |        |        |        |        |         |         |         |         |         |         |         |         |         |         |         | X       |                         |         | X                       |
| Blood pregnancy
test                                          | X                         |                               |        |        |        |        | X      |        |        |         |         |         | X       |         |         |         |         |         |         |         | X       |                         |         | X                       |
| Thyroid function                                                 | X                         |                               |        |        |        |        |        |        |        |         |         |         |         |         |         |         |         |         |         |         | X       |                         |         |                         |

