##### **5.4.2 Childbearing age**

Female subjects of childbearing potential who are sexually active with a non-sterilized male partner, and non-sterile male subjects who are sexually active with a female partner of childbearing potential must use at least 1 acceptable effective method of contraception from screening until 8 weeks after the last dose and should discuss the discontinuation of contraception with a responsible physician after that time point.

Women were considered postmenopausal after 12 months of menopause without an alternative medical cause. The requirements according to age are as follows:

- Women  $\geq 50$  years of age are considered postmenopausal if they have been amenorrheic for 12 months or more after cessation of exogenous hormone therapy and their luteinizing hormone and follicle-stimulating hormone levels are in the accepted postmenopausal range.
- Women  $< 50$  years of age were considered postmenopausal if they had been amenorrheic for 12 months or more after cessation of all exogenous hormonal therapy, had been oophorectomized with the last menses occurring  $> 1$  year earlier with radiation therapy, had been amenorrheic with the last menses occurring  $> 1$  year earlier with chemotherapy, or had been surgically sterilized (bilateral oophorectomy or hysterectomy).

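### In Cohorts 4 and 5 the last scheduled pregnancy test for completers comes 7 days after the last dose, leaving 49 of the 56 days of required post-dose contraception without one

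*Protocol*

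**What the plan says.** Section 4.3 of the protocol sets the contraception period: "Men or women of childbearing potential must use contraception during the study and for 8 weeks after the last dose". Section 5.4.2 repeats it, running from screening "until 8 weeks after the last dose and should discuss the discontinuation of contraception with a responsible physician after that time point". That discussion falls after the 8 weeks and no test is attached to it.

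The schedule tables fix when tests are done:

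- **Table 4 (Cohort 4).** The row "Blood pregnancy test 11" is marked at screening, D29, D57, D85, D113 and early withdrawal. It is blank at the two follow-up visits, D134 and D162. The row "Laboratory tests 7" has the same marks plus D162.
- **Table 6 (Cohort 5).** The pregnancy-test row is marked at screening, D29, D57, D85 and early withdrawal, and is blank at D106 and D134. The laboratory row has the same marks plus D134.
- **Table 2 (Cohorts 1-3).** The pregnancy-test and laboratory rows match: both stop at D85 apart from early withdrawal. At the final visit the only blood sample is for immunogenicity (note 18: "and Follow-up Visit on Week 20").

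Outside the tables, section 6.2.6 asks for a test before enrolment and a repeat when pregnancy is suspected. Section 7.6 requires a pregnancy arising during drug exposure to reach the sponsor within 24 hours of awareness and to be followed to 8 weeks after delivery.

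**The concern.** The protocol treats the 8 weeks after the last dose as a period in which pregnancy should be avoided, yet scheduled testing for completers stops after the first of those weeks. Tables 4 and 6 pair every scheduled laboratory panel with a pregnancy test except at the final visit, and no reason is given. The result is uneven: a woman who withdraws early is tested at her exit visit, while a woman who takes every dose is not tested at hers.

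Safety is the primary objective, and the duties in section 7.6 can begin only once a pregnancy is known. After D113 or D85, that depends on the subject or the site suspecting it. An unrecognised early pregnancy could pass the last visit without being reported. A test 7 days after the last dose may also be too early to show a conception close to that dose; this depends on the assay's sensitivity, which the protocol does not give. If so, no later scheduled test would pick it up.

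**Working it through.** The check is day arithmetic on the schedule tables, reading each row cell by cell against the study-day header.

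**Inputs**

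| | Cohort 4 (Table 4) | Cohort 5 (Table 6) |
|---|---|---|
| Last dose | D106 | D78 |
| Last scheduled pregnancy test, completers | D113 (±2) | D85 (±2) |
| Later visits, test row blank | D134, D162 (±3) | D106, D134 (±3) |
| Final laboratory panel | D162 | D134 |

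**Step 1: reproduce the protocol's 8 weeks.** Final visit minus last dose is 162 − 106 = 56 days in Cohort 4 and 134 − 78 = 56 days in Cohort 5. Both equal 8 × 7 = 56, so the final visit falls at the end of the contraception period.

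**Step 2: last dose to last scheduled test.** 113 − 106 = 7 days; 85 − 78 = 7 days.

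**Step 3: days after the last scheduled test.** 162 − 113 = 49; 134 − 85 = 49. As a share of the period, 49 / 56 = 87.5%.

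**Step 4: visit windows.** For Cohort 4, the interval from last test to final visit runs from (162 − 3) − (113 + 2) = 44 days to (162 + 3) − (113 − 2) = 54 days. Cohort 5 gives the same range: (134 − 3) − (85 + 2) = 44 and (134 + 3) − (85 − 2) = 54.

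**Step 5: compare with the treatment period.** From D29 the tests are 57 − 29 = 85 − 57 = 28 days apart, and 113 − 85 = 28 in Cohort 4. The nominal ratio is 49 / 28 = 1.75. With ±2 days at each end, the on-treatment interval can be 28 − 4 = 24 to 28 + 4 = 32 days, still below 44.

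**Step 6: who is concerned.** At most 12 + 12 = 24 subjects, of whom 8 + 8 = 16 receive IBI362. The number of women of childbearing potential among them is not known.

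**Cohorts 1-3.** Last dose D78, last test D85 and final visit D134 give the same 49 of 56 days. No laboratory panel is drawn at that final visit, and the 36 subjects were already enrolled when this version was written (section 3.2.1), so the practical point concerns Cohorts 4 and 5.

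**The case against.** The strongest reply is that nothing is misstated. No text requires a test at the end of the contraception period, and testing and contraception do different jobs. On-treatment tests decide whether dosing may continue; after the last dose there is no such decision left. Completers still get one test after the last dose and two later visits with physical examination and adverse event review, and section 6.2.6 covers any suspected pregnancy up to the last visit. Under section 7.6, stillbirth, spontaneous abortion, fetal anomaly and medically induced abortion are serious adverse events, and drug-related ones learned of after the study must still be reported. How many of the 49 days count as exposure depends on elimination data that are not shown.

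Much of this stands. There is no contradiction, the safeguards reduce the gap, and the 28-day spacing is a comparison from the treatment period, not a standard the protocol sets for follow-up. The 87.5% and 1.75 describe the calendar and do not measure risk: a test detects conceptions that came before it and does not cover days. What the reply does not supply is a scheduled test for a completer who conceives around or after her last dose. The serious adverse event rules act only once an adverse outcome has occurred and become known.

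**Conclusion.** The point holds as a minor weakness in the safety schedule. In both cohorts, scheduled testing for completers ends on day 7 of a 56-day contraception period, with 49 days (44 to 54 with visit windows) to a final visit that has a laboratory panel but no pregnancy test.

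The day counts rest only on the schedule tables. Their clinical weight rests on the 8-week margin, which is the protocol's own precaution and not evidence that drug is present throughout. The number of exposed pregnancies that might be missed cannot be estimated from the protocol. No endpoint, dose-escalation rule or analysis is affected.

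**What to change.** In the blood pregnancy test row, add one mark at the final visit: V30 (D162) in Table 4 and V23 (D134) in Table 6, for women of childbearing potential in both arms. The last scheduled test then falls on day 56 after the last dose. Keep the for-cause rule in section 6.2.6, because a conception shortly before that visit may not yet be detectable; the change narrows the gap without fully closing it.

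The cost is two table entries and at most 24 assays, with no extra visit. Blood is already drawn for the laboratory panel at those visits. The protocol gives no tube type or volume for the panel or the pregnancy test, so running both on one draw is an assumption to confirm with the laboratory; if it fails, the cost is one more tube.
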